### Health economic analysis

We will undertake a detailed health economic analysis of the cost and cost-effectiveness of ablation vs liver resection for the treatment of high-risk patients with resectable CLM. The analysis can be used to evaluate whether ablation is good value for money in this patient group. Our analysis will conform to accepted economic evaluation methods [42]. The RCT is powered to show that ablation is non-inferior to surgical resection. There is clear evidence that cost-minimisation analyses in non-inferiority studies are inappropriate [43, 44]; therefore, we will undertake an incremental cost-effectiveness analysis. We will estimate cost-effectiveness during the ‘within-trial’ period (two years/within-trial analysis) and also over the expected lifetime of the patient (lifetime/long-run analysis). The within-trial analysis will be based on resource use, health-related quality of life and survival data collected in the trial; the long-run analysis will be based on a decision-analytical model constructed using trial data supplemented with data from published sources. In the within-trial analysis, quality-adjusted life-years (QALYs) will be calculated for each patient based on the survival data and health-related quality of life data collected during the trial. The latter will be based on the EQ-5D-5 L (www.euroqol.org), which will be collected at baseline and at 3, 6, 12, 18 and 24 months post randomisation. Patient-specific utility profiles will be constructed assuming a straight-line relation between each of the patient’s EQ-5D scores at each follow-up point. The QALYs experienced by each patient from baseline to two years will be calculated as the area underneath this profile. The within-trial cost analysis will be based on volume of resource use data collected for each patient during the trial. Costs will be measured from the NHS and personal social services (PSS) perspective. Cost components included in the analysis will consist of the detailed cost of the ablation procedures (including annuitised capital costs plus consumables), laparoscopic and open surgical resection procedures, the costs of treating the complications of these procedures, CT scans and other imaging tests, MDT meetings, costs of chemotherapy, contacts for receipt of chemotherapy, contacts and medications for treating the side effects of chemotherapy, plus other resource use associated with the cancer and its sequelae (e.g. outpatient attendances, hospital readmissions, palliative care, primary care contacts, prescribed medications, use of social services including hospice care). The volume of resource use for each cost component will be measured directly in the trial from patient records and using patient diaries; unit costs will be taken from standard published sources. Patient level resource use data will be multiplied by the unit costs and summed across all cost components to calculate total costs per patient over the two-year period.

Multiple imputation by chained equations will be used to deal with missing EQ-5D and resource use values. Subsequent analyses of imputed data will include variance correction factors to account for additional variability introduced into parameter values due to the imputation process.

Cost-effectiveness will be calculated as the mean cost difference between ablation and surgical resection divided by the mean difference in outcomes (DFS/QALYs) to give the incremental cost-effectiveness ratio (ICER). Non-parametric methods for calculating confidence intervals around the ICER based on bootstrapped estimates of the mean cost and QALY differences will be used [45]. The bootstrap replications will also be used to construct a cost-effectiveness acceptability curve, which will show the probability that use of ablative therapy is cost-effective at two years for different values of the NHS’ willingness to pay for an additional QALY, and a cost-effectiveness confidence ellipse. We will also subject the results to extensive deterministic (one-, two-way, multi-way, threshold) sensitivity analysis.

In the lifetime model, cost-effectiveness will be calculated in terms of the incremental cost per QALY gained. We will undertake a review of the Cost-Effectiveness Analysis (CEA) Registry (https://healtheconomics.tuftsmedicalcenter.org/cear4/home.aspx) and the NHS Economic Evaluation Database (NHS-EED, www.crd.york.ac.uk/) to identify previous economic models that might be adapted. We will then develop a new cost-effectiveness model that will be populated based on available evidence, including the data collected during the trial. Following decisions about model structure, a list of parameter estimates required for the model will be developed. The specific details of the data to be used to populate the model will be determined following the development of the structure and the systematic searches of the literature to identify existing models. We will undertake deterministic and probabilistic sensitivity analysis, the latter assuming appropriate distributions and parameter values [46]. As part of this, we will construct cost-effectiveness acceptability curves and cost-effectiveness confidence ellipses.

We will use the numerator of the ICER described above to calculate the budget impact of using ablation compared with surgical resection, multiplying the incremental cost (positive or negative) by the estimated eligible population size. We will also undertake a value-of-information study [46] to measure the maximum amount to money the NHS should be willing to pay for additional research to reduce uncertainty regarding the use of ablation vs surgical resection in this patient group.

### Qualitative sub-study

Recruitment to RCTs with very different treatment arms can be difficult and recruitment to surgical trials is particularly challenging [47]. Qualitative research can identify aspects of the trial design that hinder recruitment and identifying possible solutions [48, 49]. Studies show patient-related (difficulties of informed consent, understanding randomisation and preference for certain treatments) and clinician-related factors (concern about impact on the doctor–patient relationship, clinical equipoise, how trial is presented to patient) affect recruitment [48–51]. The current trial compares thermal ablation and surgery for liver metastases, so it is essential to understand and address barriers to recruitment in order to demonstrate our ability to undertake the main trial.

#### Aims

To qualitatively explore patient and clinician acceptability of the trial and recruitment processes to assist in optimisation of recruitment and follow-up strategies employed for the remainder of the trial.

#### Objectives

To qualitatively explore patients and clinicians’ acceptability of the trial to assist in optimisation of recruitment strategies employed for the definitive trialExplore reasons for participation and non-participation of eligible patientsUnderstand patients’ experience of the randomisation process on decision-makingUnderstand why people refuse to participate or do not take up allocated treatmentPatient understanding of trial materials, i.e. do patients understand what will happen if they take part and do they understand what they are being randomised toAcceptability of study proceduresAcceptability of randomisationExplore clinical equipoise in the liver surgery communityUnderstand how information is presented to recruiters. In particular, explore the content and style of delivery and feed this back promptly to recruiters to improve practice

#### Method

##### Design: semi-structured interviews

A purposive sample of up to 20 patients will be recruited over nine months from across the pilot study sites, to include the three outcomes of consent: (1) participant consented and accepted treatment allocation; (2) participant consented to randomisation but refused the allocated treatment; (3) participant refused participation in the trial. In-depth, semi-structured interviews will explore patient perspectives of treatment, their understanding of the two treatments, reasons for taking part or refusing the trial and the acceptability of randomisation between the procedures.

A purposive sample of approximately 15 healthcare professionals (local principal investigators, recruiters) from across the pilot study sites will be interviewed. Participants will be selected on the basis of their ability to shed light on the recruitment process (initial discussion, recruiter interview). Interviews will explore their views about the trial, clinical equipoise and their understanding of the recruitment challenges.

Patient and staff interviews will be informed by a topic guide developed in conjunction with PPI representatives and informed by the literature. All interviews will be audio-recorded with permission.

Participant information sessions (recruiter encounters) will be audio-recorded (with permission) to examine how information is presented by recruiters and received and understood by patients, to identify issues potentially affecting trial recruitment. Information gleaned from the interviews and listening to the participant information sessions will inform the development of training materials for the main trial.

##### Data analysis

All interviews will be professionally transcribed verbatim and managed usingNVivo [52]. The data will be analysed using thematic analysis [53, 54] and coded independently by two researchers for emerging themes who will then compare codes and themes and resolve any disagreements by consensus. The analysis will be further refined by using constant comparison and contrastive approach, and looking for negative cases. A subset of up to 60 patient recruitment encounters (audio recordings of recruitment encounters) will be analysed using content analysis to identify potentially directive uses of language and good practice.

Information gained will be utilised to optimise patient information provided relating to the study (recruitment interview and PIS) and to advise clinical staff about how to describe the study, which will enable recruitment to be maximised in the main trial. Our own STAR trial [50] has confirmed the value of such approaches in improving recruitment. Emerging issues related to trial design and conduct that may be responsible for poor recruitment will be discussed with the trial team and a plan to improve recruitment during the pilot trial will be introduced if necessary. This may include reconsideration of eligibility criteria, redesign of study information, advice about presenting the study, discussions about equipoise or evidence, which may be addressed by changes to study information, protocol or training for recruiters.

## Discussion

With the development of new technologies, new methods for cancer treatment are being introduced into the healthcare market and need to be evaluated in terms of both efficacy and cost-effectiveness in comparison to competing therapies. Unless this is performed, newer, more cost-effective therapies will not be introduced into the NHS or costly treatments which are ineffective may be adopted. This problem applies at the present time with the recent introduction of thermal ablation techniques as an alternative to surgery for the treatment of patients with CLM. If effective, they should be more widely implemented in the NHS and the technology refined. If they are ineffective, support for more extensive surgery is required and the technology should be abandoned. It is important that any evaluation of effectiveness and cost-effectiveness between competing therapies should be based on RCTs, which ensure that similar types of people receive the two therapies. In addition, the inclusion criteria and exclusion criteria should be such that it should be possible to perform both therapies in an adequate way in order to maintain equipoise and to avoid a therapy being considered superior to another because of the selection of participants to be included in the trial. In the LAVA trial, we will include only participants who are eligible for ablation and surgery. Although we have left it for the local specialist MDT to make the decision as to whether the potential participant is eligible for both ablation and surgery, we anticipate that the participants included meet the CIRSE criteria for RFA for CLM, i.e. ≤ 5 lesions and tumour size does not exceed 3 cm at its longest axis [16].

Controversies in cost-effectiveness are frequently addressed through an NIHR-funded HTA. A recent report on clinical effectiveness and cost-effectiveness of ablative therapies in the management of liver metastases suggested that a trial investigating the effectiveness and cost-effectiveness of ablation vs surgery in patients with resectable CLM is necessary [25]. The long-term results of ablation and surgery can be considered equivalent only if the difference in long-term survival between the modalities is < 4 months due to the recovery period required following major liver surgery. However, the true difference in cancer survival between ablation and surgery in patients with CLM is not known.

‘NHS England Strategic and Operational Planning 2014 to 2019’ states the following ‘The healthcare system is facing the challenge of significant and enduring financial pressures. People’s need for services will continue to grow faster than funding, meaning that we have to innovate and transform the way we deliver high quality services, within the resources available, to ensure that patients, and their needs, are always put first.’ Clearly, it is important to maximise the health of people using the resources available.

This research will achieve this purpose of maximising the health of people using the resources available. The results of this research can be adopted immediately in the UK because of widespread availability of expertise in both thermal ablation techniques and liver resection surgery, resulting in maximisation of the health benefits using the resources available in a short period of time for high-risk patients with potentially resectable CLM. This research may also have indirect benefit for low surgical risk patients with CLM in the long term. The results of the current research will either justify the concerns of clinicians who consider that thermal ablation is inferior to surgery for the treatment of patients with CLM (in which case, no RCT comparing ablation and surgery will be conducted in low surgical risk patients as it is extremely unlikely that ablation is equivalent or better than surgery in low surgical risk patients if it offers worse results than surgery in high surgical risk patients) or it may reassure clinicians that ablation is an effective therapy in which case, a subsequent RCT may be conducted in low surgical risk patients.

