### Participants

The trial will recruit 330 high surgical risk patients eligible for liver resection (165 in each arm). High-risk patients are defined as any patients that meet at least one of the following criteria: considered high-risk due to age (e.g. > 75 years); major co-morbidities as judged by the treating clinician; liver metastases with poor prognosis or high-risk surgery due to the tumour burden.

Patients will be identified for trial eligibility at the specialist liver multi-disciplinary treatment (sMDT) meeting. Suitability for inclusion into the trial will be assessed according to the following eligibility criteria.

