#### Inclusion/exclusion criteria

Inclusion criteriaAge ≥ 18 yearsAble to provide written informed consentMDT diagnosis of colorectal liver metastases considered to be resectable or ablatable with curative intentResected colorectal primary or plan for primary resection with curative intentMeets *one or more* of the following criteria:Considered high-risk for surgery due to age (based on local policy)Major co-morbidities as judged by the treating clinician. Examples include history of myocardial infarction, severe chronic airway disease, major cerebrovascular accidents (CVA), pulmonary embolism (PE)Liver metastases with poor prognosis and high-risk surgery due to tumour burdenExamples include extensive synchronous disease, need for two stage resection or ALPPS, small anticipated remnant liver volume, curable extra-hepatic disease, downstaged with chemotherapy, poor response after chemotherapy but still resectable or ablatableSuitable candidate for either liver resection surgery or thermal ablation as judged by the MDTAble and willing to comply with the terms of the protocol including health-related quality of life (HRQoL) questionnaires

Exclusion criteriaIncurable extra-hepatic metastasesNot a suitable candidate for liver resection surgeryNot a suitable candidate for thermal ablationConcurrent malignant disease (except basal cell carcinoma)Patients who have undergone previous surgery or ablation for CLMPlanned simultaneous resection of primary and liver metastasesPregnancy

All patients will provide written informed consent. Patients will then be randomised on a 1:1 basis to receive either thermal ablation or surgical resection. A computer-generated minimisation programme that incorporates a random element will be used to ensure treatment groups are well-balanced for the following participant characteristics:Research siteSynchronous/metachronous diseasePrimary cancer in situ (Yes/No)High-risk for surgery due to age (Yes/No)Major co-morbidity (Yes/No)Poor prognosis or high-risk surgery due to tumour burden (Yes/No)Largest lesion size ≤ 5 cm (Yes/No) [13]Planned surgical resectionOpenLaparoscopicPlanned ablative treatmentRFAMWA

Blinding will not be performed.

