### Intervention: thermal ablation (RFA or MWA)

#### Definition of the intervention in the ablation arm

For patients in the ablation arm, the intervention is defined as the collection of ablation sessions conducted as treatment for the index disease (as defined above). Either RFA or MWA will be carried out according to the local availability of equipment and expertise. Ablation may also be performed at laparoscopic or open surgery if the percutaneous approach is contraindicated. Minimum standards for delivery of ablation to be achieved during the trial will be agreed by all centres in a pre-trial standardisation meeting.

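### The tumour-burden criterion reads *and* in one place and *or* in two, and the 5 cm lesion-size factor says little about a population expected not to exceed 3 cm

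*Protocol article*

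**What the plan says.** **Tumour burden.** Under Participants, one of the three ways to count as high-risk is "liver metastases with poor prognosis or high-risk surgery due to the tumour burden". In the section Inclusion/exclusion criteria, the inclusion list gives the same criterion with *and* between the two features, followed by examples. The minimisation list in that section returns to *or*: "Poor prognosis or high-risk surgery due to tumour burden (Yes/No". Both the definition and the inclusion list need only one of the three risk criteria (age, co-morbidity, tumour burden) to be met.

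**Lesion size.** The minimisation list contains "Largest lesion size ≤ 5 cm (Yes/No". On the expected population, the Discussion says "we anticipate that the participants included meet the CIRSE criteria for RFA for CLM". Those radiofrequency criteria allow at most five lesions and require that "tumour size does not exceed 3 cm at its longest axis". The same sentence makes clear that this is not a rule: "we have left it for the local specialist MDT to make the decision as to whether the potential participant is eligible for both ablation and" the surgical option. The inclusion and exclusion lists set no size limit. On modality, "Either RFA or MWA will be carried out according to the local availability of equipment and expertise". The Statistical analysis section adjusts the primary survival model for the stratification factors, which I take to be the minimisation factors.

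**The concern.** The first matter concerns who may enter. For a patient with no age or co-morbidity risk, the connector decides eligibility. With at least 20 sites planned and the decision left to local teams, two readings of one criterion can be applied side by side. The minimisation factor carries nearly the same name as the entry criterion but uses the other connector, so the two can be coded differently for the same patient. The factor then enters the primary model.

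The second matter concerns efficiency. The designers judged lesion size worth balancing and adjusting for, but placed the cut above the range that they expect to enrol. A factor with almost everyone in one level does little in the allocation or in the model.

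**Working it through.** **1. The connector.** Take the possible patients with no age or co-morbidity risk:

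| Features present | Inclusion list (*and*) | High-risk definition (*or*) | Minimisation factor (*or*) |
|---|---|---|---|
| Both | eligible | eligible | Yes |
| Poor prognosis only | not eligible | eligible | Yes |
| High-risk surgery only | not eligible | eligible | Yes |
| Neither | not eligible | not eligible | No |

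The two middle rows conflict. A patient who enters on age or co-morbidity is eligible either way. With just one tumour-burden feature, however, that patient fails the tumour-burden entry criterion and is still coded Yes on the factor. The document gives no figure for how many patients fall in these rows.

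**2. The sample size, to see whether it is touched.** Inputs from Sample size calculations: 14 months in the resection arm, a four-month margin, 80% power, one-sided 2.5%, four-year accrual, two-year follow-up, 5% drop-out. Assumptions: 14 months is an exponential median, the margin is 14 against 10 months (hazard ratio 1.4), both arms are truly at 14 months, accrual is uniform, and everyone is followed to 24 months after the last entry.

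- Events (Schoenfeld): 4 × (1.960 + 0.842)² / (ln 1.4)² = 278.
- Event probability 0.8837, so 278 / 0.8837 = 315 patients.
- 315 / 0.95 = 332, close to the stated 330. Variants of the formula and of the event rate give 322 to 338.

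The result does depend on the follow-up assumption: if each patient stops at 24 months, the same steps give 422. That is a separate matter. Lesion size appears nowhere in the calculation, so the cut does not alter it.

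**3. What the 5 cm factor does.** If every lesion is at most 3 cm, all 330 patients fall in one level, and the factor separates nobody and drops out of the model. If local teams enter larger lesions, it works. The share above 5 cm is not in the document, so 0 to 20% is assumed. I used an illustrative Pocock–Simon minimisation: 330 patients, 20 sites, biased coin 0.8, assumed prevalences for five further binary factors, 400 runs per setting. The mean absolute difference between arms in the number of patients above 5 cm was:

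| Assumed share above 5 cm | Patients | Without the factor | With the factor |
|---|---|---|---|
| 0% | 0 | 0 | 0 |
| 2% | about 7 | 2.0 | 1.3 |
| 5% | about 17 | 3.3 | 1.6 |
| 10% | 33 | 4.6 | 1.7 |
| 20% | 66 | 5.9 | 1.8 |

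Whatever the share, patients at or below 3 cm and those between 3 and 5 cm are treated alike.

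**4. Scale of what an unadjusted size effect could do.** No prognostic effect of size is given, so this is illustration only. After drop-out, 330 × 0.95 gives about 313 patients.

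- SD of the between-arm difference in a standardised covariate: √(4/313) = 0.113.
- With an assumed hazard ratio of 1.3 per SD: 0.113 × ln 1.3 = 0.113 × 0.262 = 0.030 on the log hazard ratio, and × 1.96 = 0.058.
- Standard error of the log hazard ratio at 278 events: 2/√278 = 0.120.
- Share of variance: 0.030² / 0.120² ≈ 6%.

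The shift is proportional to the log hazard ratio per SD, so it runs from zero (no size effect) to ±0.058 at 1.3 and rescales for any other assumption.

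**The case against.** **On size.** A reader might infer that the factor balances nothing. That needs every participant to be at or below 3 cm. The 3 cm figure is an anticipation drawn from radiofrequency criteria, microwave ablation is also allowed, the local team decides, and the inclusion examples admit extensive disease. Step 3 shows better balance at each non-zero share tried. The cut also carries a literature reference, so it may have been chosen for prognosis rather than as an ablation limit; the document does not say. This stands: the factor is weak to the extent that the expectation is met, not empty by construction.

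A reader might also set 0.058 against ln 1.4 = 0.336, obtain 17%, and see a threat to the non-inferiority conclusion. That does not follow. The hazard ratio of 1.3 is assumed, 0.058 is a 95% extreme, and chance imbalance under randomisation is not bias and is already part of the standard error. Nor does the document rank size as the leading determinant of ablation success: the Radiofrequency ablation section lists it beside lesion number and nearness to ducts, bowel and large vessels.

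Further covariates can be left to an analysis plan, and the article excludes none. But it does fix adjustment for the factor as cut, so a better form of that adjustment is a fair suggestion rather than a complaint about missing detail.

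**On the connector.** The examples under the inclusion criterion steer sites towards including the patients they name, which may soften the conflict in practice. Calling any example a matter of prognosis alone or of surgical risk alone is a clinical judgement that the document does not make. Different enrolment by site is therefore possible but not shown. The contradiction in the operative text remains. It lies between the inclusion list and the other two places; the minimisation list is not itself inconsistent.

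**Conclusion.** Two points hold, of unequal weight. The tumour-burden criterion contradicts itself, with one *and* against two *or*, and this decides entry for patients with exactly one of the two features and no other risk criterion. It also lets the minimisation factor differ from the entry criterion. The number affected is unknown.

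The lesion-size point is minor. The 5 cm cut does not fit the expected population and never distinguishes sizes below 5 cm, so adjusting for it captures little of any size effect in that range. It causes no bias and leaves 330 unchanged. What could be gained is modest precision and protection against chance imbalance, about 6% of the variance under the assumed hazard ratio of 1.3 per SD and less if the effect is smaller.

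**What to change.** 1. Reconcile the tumour-burden wording so that the definition under Participants, the inclusion list and the minimisation factor use one connector. Which one is for the investigators to decide. The cost is essentially a one-word correction, best made before further patients enter.
2. Pre-specify largest lesion diameter as a continuous covariate in the primary disease-free survival model, in addition to the minimisation factors. Take it from the pre-randomisation imaging on which the size factor was coded. Size must already be known to run the minimisation, and a baseline staging CT is already mandatory, so no new assessment is needed; the cost is analysis-plan wording and recording the diameter instead of only Yes/No.
3. Changing the minimisation cut is optional and unnecessary once the covariate is in. It would need a system update, and a cut exactly at 3 cm could be as uninformative as the present one if no lesion exceeds 3 cm.
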